### Study population

Eligible patients must be between 6 months and less than 18 years of age with ED clinician diagnosed Bell’s palsy with onset less than 72 hours before randomisation. ED clinicians will follow local guidelines in the diagnosis of Bell’s palsy. Participants must fulfil all of the inclusion criteria and none of the exclusion criteria (Table 1).

**Table 1 Tab1:** Inclusion and Exclusion Criteria

Inclusion criteria	
1. Be aged from 6 months to less than 18 years of age.	
2. Weight ≥5 kg.	
3. Be diagnosed with Bell’s palsy by their treating doctor.	
4. Have acute onset of symptoms of Bell’s palsy for less than 72 hours prior to randomisation.	
5. Have written informed consent provided by the parent(s) or legal guardian. The participant, where he/she is deemed competent to provide consent, may also provide written consent.	
Exclusion criteria	
1. Likely to be unable to complete the 1 month study assessment of Bell’s palsy symptoms. Where the participant is unable to attend the study site, the assessment can be completed via videoconferencing using skype software or other online tools.	
2. Previously randomised into the study.	
3. Contraindication to prednisolone, including: active or latent tuberculosis, systemic fungal infection, known hypersensitivity to prednisolone or any of the excipients in the liquid, diminished cardiac function, diabetes mellitus, peptic ulcer or chronic renal failure, multiple sclerosis, recent active herpes zoster or chickenpox.	
4. Use of any systemic or inhaled steroid within 2 weeks prior to the onset of symptoms.	
5. Current or past oncological diagnosis.	
6. Pregnancy.	
7. Breast feeding.	
8. Currently receiving concomitant medications in which prednisolone is contraindicated.	
9. Immunisation with a live vaccine within the previous 1 month.	
10. Requirement for a live vaccine within 6 weeks of the first dose of study drug.	
11. Signs of upper motor neurone VII nerve palsy (weakness of the lower half of the face only).	
12. Diagnosis by a medical doctor of acute otitis media concurrently or within 1 week prior to the onset of Bell’s palsy symptoms.	
13. Evidence of vesicles on the ear drum suggestive of herpes zoster related Ramsay Hunt syndrome.	
14. Known facial trauma within 1 week prior to the onset of symptoms that in the view of the clinician may have caused or contributed to facial palsy.	
15. Any other condition at risk of being influenced by the study treatment or that might affect completion of the study.	
16. Any concern regarding parent/guardian/participant ability to comply with the study protocol.	
17. Prior episode of Bell’s palsy.	

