**Methods/Design:**

We are conducting a randomised, triple-blinded, placebo controlled trial of the use of prednisolone to improve recovery from Bell’s palsy at 1 month. Study sites are 10 hospitals within the Australian and New Zealand PREDICT (Paediatric Research in Emergency Departments International Collaborative) research network. 540 participants will be enrolled. To be eligible patients need to be aged 6 months to < 18 years and present within 72 hours of onset of clinician diagnosed Bell’s palsy to one of the participating hospital emergency departments. Patients will be excluded in case of current use of or contraindications to steroids or if there is an alternative diagnosis. Participants will receive either prednisolone 1 mg/kg/day to a maximum of 50 mg/day or taste matched placebo for 10 days. The primary outcome is complete recovery by House-Brackmann scale at 1 month. Secondary outcomes include assessment of recovery using the Sunnybrook scale, the emotional and functional wellbeing of the participants using the Pediatric Quality of Life Inventory and Child Health Utility 9D Scale, pain using Faces Pain Scale Revised or visual analogue scales, synkinesis using a synkinesis assessment questionnaire and health utilisation costs at 1, 3 and 6 months. Participants will be tracked to 12 months if not recovered earlier. Data analysis will be by intention to treat with primary outcome presented as differences in proportions and an odds ratio adjusted for site and age.

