#### Baseline assessment and randomisation during the ED visit

Following informed consent, eligibility check and randomisation, demographics and relevant clinical information will be collected from the patient including side of the palsy, onset and associated symptoms, relevant past medical history, and medical evaluations/contacts prior to the ED visit.

Study assessments regarding the severity of facial palsy as measured by the HB and Sunnybrook scales and facial imaging (digital video recording and still photographs) will be conducted using standardized instructions based on the study by Sullivan et al. [36]. A camera will be provided to all study sites. The images will be assessed at a later time point by assessors blinded to the study treatment assignment for quality control purposes.

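### The steroid exclusion in Table 1 ends at symptom onset and disagrees with the abstract, so steroid taken between onset and randomisation (up to 72 hours) is not clearly excluded

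*Protocol article*

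**What the plan says.** Under Study population, the protocol article requires every participant to meet all the inclusion criteria and none of the exclusion criteria in Table 1, so that table decides entry.

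- **Inclusion criterion 4:** "Have acute onset of symptoms of Bell’s palsy for less than 72 hours prior to randomisation".
- **Exclusion criterion 4:** "Use of any systemic or inhaled steroid within 2 weeks prior to the onset of symptoms". The look-back is counted from onset and ends there.
- **Abstract, Methods/Design:** "Patients will be excluded in case of current use of or contraindications to steroids or if there is an alternative diagnosis". Table 1 has no item on current steroid use.
- **Baseline assessment and randomisation during the ED visit:** the history taken includes "relevant past medical history, and medical evaluations/contacts prior to the ED visit". The text places this collection after consent, the eligibility check and randomisation, and does not say that steroid exposure is recorded.

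The Background reports that steroid use in children with this condition varies between centres. The Interventions section says that prednisolone is the steroid most often used for it in children.

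**The concern.** The interval between onset and randomisation is when another clinician would start a steroid for this palsy. As Table 1 is written, a child treated in that interval meets no exclusion that names the treatment, while under the abstract a child still taking the steroid would be excluded. Two sites, each following one of the two places, could enrol different children.

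The stake is the contrast between the arms. A pre-treated child allocated to placebo has already had some of the active treatment, and under the intention-to-treat analysis stays in the placebo arm. The observed difference then moves toward zero. The design has little room for this, because its evaluable number per arm sits almost exactly at the 80 % power requirement.

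**Working it through.** **Step 1. Is there an item that closes the gap?** The candidates in Table 1 are:

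| Table 1 exclusion item | What it covers | Names steroid taken after onset? |
|---|---|---|
| 3 | Contraindications to prednisolone | No |
| 4 | Systemic or inhaled steroid, 2 weeks before onset | No, ends at onset |
| 8 | Current medicines with which prednisolone is contraindicated | No |
| 15 | Other conditions that treatment might influence or that might affect completion | No |
| 16 | Concern about ability to comply | No |

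Criterion 8 is worded for the present, and criterion 12 (otitis media) covers both the present and the week before onset. Criterion 4 has no such extension.

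**Step 2. Reproduce the plan's sample size.** Inputs from Sample size estimation: placebo 60 %, prednisolone 72 %, two-sided α = 0.05, 80 % power. Two-proportion z-test with pooled variance under the null and no continuity correction, p̄ = 0.66:

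n = [1.960·√(2·0.66·0.34) + 0.842·√(0.60·0.40 + 0.72·0.28)]² / 0.12² = 243.4, rounded up to **244 per group**. This is the stated figure, and power at 244 is 80.1 %.

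The recruitment target of 270 per group less 10 % loss leaves 270 × 0.90 = 243 evaluable, where power is 79.9 %.

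**Step 3. Dilution scenarios.** Assumptions, none of them in the documents:

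- A share q of children in both arms had steroid between onset and randomisation.
- A pre-treated placebo child gains a fraction e of the 12-point effect (e = 1 full, e = 0.5 half).
- The prednisolone arm stays at 72 %.

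The placebo rate is then p₁ = 0.60 + 0.12·e·q, the true difference is d = 0.72 − p₁, and

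power = Φ{ [d·√243 − 1.960·√(2p̄(1−p̄))] / √(p₁(1−p₁) + 0.72·0.28) }, with p̄ = (p₁ + 0.72)/2.

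Worked case, q = 10 % and e = 1: p₁ = 0.612, d = 0.108, p̄ = 0.666. The numerator is 1.684 − 1.960·0.667 = 0.376 and the denominator is 0.663, so power = Φ(0.568) = 71.5 %.

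| Exposed share q | Difference, full effect | Power, full effect | Difference, half effect | Power, half effect |
|---|---|---|---|---|
| 0 % | 12.0 points | 79.9 % | 12.0 points | 79.9 % |
| 2 % | 11.8 | 78.4 % | 11.9 | 79.2 % |
| 5 % | 11.4 | 75.9 % | 11.7 | 78.0 % |
| 10 % | 10.8 | 71.5 % | 11.4 | 75.9 % |
| 20 % | 9.6 | 61.6 % | 10.8 | 71.5 % |

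**The case against.** The strongest reply is that the abstract shows the intent. A child on a continuing steroid course is the main worry, and the abstract excludes that child. On this view the fault is a mismatch in wording, not a decision to admit pre-treated children. Investigators also have some discretion through the open-ended list in criterion 3 and through criterion 16, and a condensed article may leave the handling of open-label steroids to the full protocol. The intent is fair to credit. It does not settle the matter, because the entry rule points to Table 1, the abstract's exclusion has no counterpart there, and a child who took a dose and stopped may fall outside both.

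The second reply concerns size, and it stands. Variable steroid use between centres does not measure prescribing before the ED visit, and "medical evaluations/contacts prior to the ED visit" does not say that a steroid was given. Exposure before randomisation lasts less than 72 hours, against a 10-day study course, so assuming the full effect is the severe case. At 2 % exposure the loss is under 2 power points.

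A reader might infer that the trial fails to deliver its 80 % power, or that its sample size is wrong. The documents do not support either: 244 per group reproduces, and the lower power figures hold only under assumed exposure. Nor is there support for reading this as confounding or a false-positive risk, since pre-treatment precedes blinded 1:1 allocation and should balance between arms.

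**Conclusion.** The point holds as a gap in the eligibility criteria and a disagreement between Table 1 and the abstract. As written, a child already given steroid for this palsy can be enrolled under Table 1. The direction of any effect is toward no difference.

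The amount is not known. Across the scenarios shown, power ranges from nearly unchanged (79.2 % with 2 % exposed and half effect) to materially reduced (61.6 % with 20 % exposed and full effect). That range rests on the assumed share, the assumed effect of pre-treatment and a prednisolone arm held at 72 %. The case for acting rests on the inconsistency and the low cost of removing it, not on any one power figure.

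**What to change.** Reconcile Table 1 with the abstract so that the steroid exclusion runs up to randomisation: the 2 weeks before onset, as now, plus any use from onset to randomisation, whether continuing or stopped. This is a one-line amendment, and the article states that the trial is still recruiting. The cost is that some pre-treated children become ineligible. Their number is unknown, and if it is not small, recruitment will slow.

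For children already enrolled, the remedy is conditional. If steroid use before randomisation was captured, or can be retrieved from source notes, record it as a baseline characteristic in both arms by staff blind to allocation. Then add a sensitivity analysis of the primary outcome that excludes those children. Because the exposure precedes randomisation, this keeps the randomised comparison intact within the remaining children. The intention-to-treat analysis of all randomised participants stays primary. The cost is a notes check and one additional analysis.

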### Randomisation

Participants will be randomized in a 1:1 ratio to one of two treatment arms: intervention (prednisolone) or matched placebo. An independent statistician has generated a randomization schedule using variable block sizes, stratified by site. This schedule will be used by the central study pharmacist at RCH to undertake the blinding, labelling and distribution of the study drugs to participating sites by putting together study packs of the required drug labelled with sequential study numbers for each site and dosing instructions. Randomization will be undertaken at the site by ED and research staff by selecting the lowest numbered study pack (next pack system) from the study drug store in ED.

### Interventions

There is currently little evidence to assist in determining the best prednisolone dose in children. Adult studies of Bell’s palsy have used various steroids and doses [17–19, 29, 49]. The two large adult RCT used 50 mg prednisolone daily for 10 days [18] or 60 mg prednisolone daily for 5 days then weaning over 5 days [19]. The only paediatric RCT of steroid use for Bell’s palsy used methylprednisolone 1 mg/kg/day (equivalent to 1.25 mg/kg/day prednisolone) for 10 days, then weaned over 3–5 days [12]. Observational data from the central study site [4], and unpublished survey data from the PREDICT network indicate that prednisolone is the most frequently used steroid for Bell’s palsy in children, usually at a dose of 1 mg/kg/day for a variable number of days. Prednisolone is also the most frequently used oral corticosteroid in children in Australia and New Zealand for various other inflammatory conditions, with routine doses of 1–2 mg/kg/day.

Noting the adult dose used by Sullivan et al. [18] (50 mg for 10 days without taper); having sought advice from endocrinologists and rheumatologists; in consideration of the current local guidelines [50] and with consideration to ease of preparation of study drugs, a dose of ~1 mg/kg daily for 10 days without taper was chosen for the current study. For the 10-day study treatment period, participants will therefore be assigned to receive either ~1 mg/kg/day of prednisolone (based on weight categories) up to a maximum of 50 mg/day or to receive matching placebo.

Adverse events from this dose and short duration are expected to be limited to minor behavioral changes and possible weight gain. Drug related adverse events will be recorded. Risks should be reduced by adherence to inclusion and exclusion criteria listed above.

Randomization will be blinded so that trial participants, the investigator team (including the facial image assessors), data management staff, data analysis staff and any other clinical staff remain unaware of the study arm to which trial participants have been assigned to. Only the central pharmacist at RCH and the independent statistician who generated the randomisation list will be unblinded.

Prednisolone will be supplied as Redipred® oral liquid. Redipred® contains the active ingredient prednisolone sodium phosphate 6.72 mg/mL (equivalent to prednisolone 5 mg/mL). The look- and taste-matched placebo will be supplied in 30 mL plastic bottles. The Redipred® and matching placebo will be supplied by Aspen Pharmacare Pty Ltd (St Leonards, NSW, Australia).

All participants will receive the study drug (prednisolone or placebo) orally in liquid form. Participants will receive the number of milliliters required per day based on a pre-calculated weight-based table. The study drug will be prescribed as a once daily dose.

The central pharmacist at RCH will blind and label the bottles of prednisolone and placebo and place them into study packs. The central pharmacist at RCH will provide each site’s clinical trial pharmacy with sufficient stock to cover the site’s projected recruitment, co-ordinate ongoing resupply of study medication, ensure in-date supplies are available at each site and oversee drug accountability. Study packs will be kept in each site’s ED in a locked, limited-access facility available for immediate use for participant randomisation.

At the time of randomisation, the senior staff member or medically qualified investigator in the ED will select the lowest numbered study pack available from the study drug store and arrange the first dose of the study drug to be administered in the ED by a clinical nurse. The parent/guardian/participant will be provided with the remaining study drug along with instructions regarding dosing and storage.

#### Adherence/Compliance

Compliance/adherence will be assessed as part of the Day 14 assessment. Families will be instructed to return all study drug bottles at the 1 month study clinic visit when the remaining liquid in the bottles will be measured.

#### Concomitant care

All parent/guardian/participants will be provided with a study alert card for non-study health care professionals providing care during the study.

#### Emergency unblinding

The randomisation code for an individual participant may only be unblinded in emergency situations, where the investigator decides a participant cannot be adequately treated without knowing the identity of their treatment allocation. The randomisation code is held at the central pharmacy at RCH.

### Study procedures and assessments

#### Recruitment and consent

In the event of the presentation of a child with suspected Bell’s palsy ED staff at participating sites will be asked to notify the senior medical doctor on duty who will perform an initial assessment of potential eligibility. If potentially eligible, the senior doctor or a member of the investigator team will approach the participant and their parent/guardian(s) to inform them of the study, determine their interest in participating, confirm eligibility and (where applicable) conduct the written informed consent process.

The relevant clinical teams at each site will receive standardized, study specific education based on centrally developed study education materials. Notification letters about the study will be sent to relevant physicians with consultation or referral roles at study sites.

### Study procedures

An overview and the timing of the study procedures are outlined in detail in Table 2.

**Table 2 Tab2:** Assessment Schedule BellPIC Study

Procedure	Enrolment & Randomisation Time point 1	Time point 2	Time point 3	Time point 4	Time point 5	Time point 6
	Day 1	Day 14^a^	Month 1^b^	Month 3^b^	Month 6^b^	Month 12^d^
Obtain Informed consent	✓					
Collect demographic and relevant information	✓					
Facial images	✓		✓	✓	✓	
House Brackmann [18, 27] & Sunnybrook [32, 38] scales augmented with SAQ [48]	✓		✓	✓	✓	
Review inclusion & exclusion criteria	✓					
Randomise	✓					
Study drug dispense	✓					
Study drug compliance review		✓	✓			
Adverse events review		✓	✓^e^			
Specialist clinician review			✓^c^			
Emotional and functional impact using PedsQL, CHU-9D and Harter scales [39–44]			✓	✓	✓	
Assessment of pain (VAS/FPS-R) [45–47]			✓	✓	✓	
Participant and parent perception of recovery (lay translation of HB scale)		✓	✓	✓	✓	✓
Collection of information on medical attendances			✓	✓	✓	

*HB* House Brackmann scale, *SAQ* Synkinesis Assessment Questionnaire, *PedsQL* Pediatric Quality of Life inventory, *CHU-9D* Child Health Utility 9D, *VAS* Visual Analogue Scale, *FPS-R* Faces Pain Scale Revised

^a^This assessment will be conducted over the telephone or on-line. A window of ±5 days is allowed

^b^A window of ± 7 days will be allowed to facilitate appointment scheduling for the study assessments attended on-site at 1 month; a window of ±14 days will be allowed to facilitate appointment scheduling or follow up contacts by phone, email or online for study visits or contacts at 3 and 6 months. Once a participant has been assessed to have made a complete recovery (HB score of 1), they will no longer be required to attend further visits to the study clinic and will only be required to complete questionnaires and scales by telephone, email or online at 3 and 6 months

^c^The senior specialist clinician may be a pediatric neurologist; ENT specialist; pediatrician; or ED physician

^d^This assessment will be required only for those deemed to have been not recovered at their 6 month assessment. A window of ±14 days will be allowed to facilitate follow up contacts scheduling

^e^Adverse events which are unresolved at 1 month should be followed till resolution or stabilisation

#### Baseline assessment and randomisation during the ED visit

Following informed consent, eligibility check and randomisation, demographics and relevant clinical information will be collected from the patient including side of the palsy, onset and associated symptoms, relevant past medical history, and medical evaluations/contacts prior to the ED visit.

Study assessments regarding the severity of facial palsy as measured by the HB and Sunnybrook scales and facial imaging (digital video recording and still photographs) will be conducted using standardized instructions based on the study by Sullivan et al. [36]. A camera will be provided to all study sites. The images will be assessed at a later time point by assessors blinded to the study treatment assignment for quality control purposes.

#### Follow up assessment at 14 days

Approximately 14 days after randomization, the parent/guardian/participant will receive a phone call from the study team to assess medication compliance, adverse events and ongoing palsy symptoms (as judged subjectively by the parent/guardian/participant).

#### Follow up assessment at 1 month

One month after randomization, participants will attend a visit at the study site. Where the participant is unable to attend the study site, this may be completed via videoconferencing.

A specialist clinician (a pediatric neurologist; ENT specialist; pediatrician or ED physician to accommodate site specific resources) will review the participant to: exclude an alternative diagnosis for the Bell’s palsy symptoms; determine if Bell’s palsy symptoms are still present; determine HB grade (the primary outcome) and the Sunnybrook scale of the Bell’s palsy; determine the presence of synkinesis or autonomic dysfunction using the SAQ. Facial images (video recording and still photographs) will be recorded. A questionnaire will be completed by the parent/guardian or participant (age dependent) for all participants and will elicit details on adverse events, ongoing palsy symptoms, reports of abnormal hearing, lacrimation and altered taste, date of resolution of facial palsy symptoms (if resolved) as subjectively perceived by parent and any medical contact.

The following scales and tools will be completed by the parent/guardian or participant depending on the age of the participant (varies by scale):o PedsQL and CHU-9D to assess the emotional and functional wellbeing (quality of life) of the participant.o The Harter scale to assess perceived appearance.o FPS-R or VAS to capture pain symptomso A study-specific lay translation of the HB scale

A site research assistant will collect the study drug containers from participants attending the study site for later assessment of residual volumes and return to the site pharmacy.

